### Research Aims

Considering the available evidence in the current literature and our perceived gaps in the knowledge related to our topic, in this study, we study the role of ethnicity and environment in the regulation of response to sensory stimuli among children from a neurophysiological perspective by applying the theory of allostasis. We aim to explore differences in the regulation of response to sensory stimuli in children through their ethnicity (as proxy measure of genetic influence) and environments (as a general measure of beliefs, practices, behaviors, culture, parenting practices, physical landscapes, and sociocultural and economic aspects). Specific to this manuscript, the authors also aim to determine the ample sample size needed for the main study, based on the pilot data presented.

## Methods

### Ethical Considerations

Ethical approval was obtained from the Hong Kong Polytechnic University, Human Subjects Ethics Sub-committee (Hong Kong, SAR), with reference number HSEARS20150316001, and from the University of Santo Tomas-College of Rehabilitation Science (Philippines) with protocol no: FI-2015-02. Before the data-gathering procedure, assent forms and parental consent forms will be distributed to the participants of the study and their respective parents. Whenever the discomfort could not be tolerated by the child, the testing procedure was stopped.

### Participants

Using a cross-sectional study design, this study compares the autonomic activity in different experimental conditions (resting baseline condition, stimulation condition, and recovery condition) among 4 groups of participants, comprising 2 groups of typically developing children, (1) from different ethnicities (Chinese children in Hong Kong, Filipino children in the Philippines-Urban area); (2) from different geographic environments (Filipino children in Hong Kong, Filipino children in the Philippines-Urban area); (3) from different ethnicity and geographic environments (Chinese children in Hong Kong and Filipino children in the Philippines-Urban area); and (4) from different physical environments (Philippines-Urban area, Philippines-Rural area). Participants will be typically developing boys and girls, aged 7-12 years with no known developmental, neurological, or medical condition. The sample size of n=32 for each group was initially estimated based on the mean change of ANS indices of a previous study with similar but not the same experiment [67] by using the effect size of 0.8 for group differences with the alpha level at .05.

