**Methods:**

In this study, we intend to recruit 128 children from different ethnic groups or environment contexts as follows: (1) 32 typically developing Chinese children living in Hong Kong; (2) 32 typically developing Filipino children living in Hong Kong; (3) 32 typically developing Filipino children who are living in urban areas; and (4) 32 typically developing Filipino children who are living in rural areas in Philippines. Autonomic activity (heart rate variability [HRV] and electrodermal activity [EDA]) will be measured and recorded using Polar H2 heart rate monitor and eSense GSR skin response sensor. Autonomic activity (HRV-low frequency, HRV-high frequency, and EDA) at different conditions between pairwise groupings will be tested using multivariate analysis of variance (MANOVA). All significant levels will be set at *P* ≤.05.

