Ethnicity refers to the biomedical origins and genetic similarities among individuals [21-23]. Ethnicity represents biologically embedded genetic traits and its expressions that have been suggested to influence behavioral and physiological responses related to adaptation [19]. A child’s response to sensory information within his environment seems universal and stable across ethnicities. Royeen and Mu [24] implicated no significant differences in the sensory responses between North American and multiethnic European children situated in the United States and Germany, respectively. Conversely, other researchers counter-argued and found influences of ethnicity on children’s regulation of sensory stimuli using behavioral measures [2]. Caron et al [25] obtained some differences on the responses to sensory information between North American and Israeli children in their responses to sensory experiences. Although Tirosh et al [26] suggested that ethnicity can account for significant differences in the regulation of sensory response between 2 different ethnic groups of children living in the same environment, older children from different ethnic-cultural groups exhibit differences in regulatory responses. The evidence on the influence of ethnicity on the regulation of response to sensory stimuli appears to be inconsistent and inconclusive. Furthermore, it is unclear whether such differences are influenced by inherent ethnicity or the environment in context. In this research, we look at the regulation of response to sensory stimuli among a group of children from different ethnicities, while controlling for environment variables. Specifically, to represent such ethnic differences, we recruit Hong Kong-Chinese and Filipino school-aged children living in Hong Kong and the Philippines, respectively.

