### Research Hypothesis

This research study is an exploratory inquiry on the role of ethnicity and environments in the regulation of response to sensory stimuli among children by using neurophysiological outcome measures. Supported by behavioral studies and the concept of allostasis as applied in this research, the researchers hypothesize that there is significant difference in the regulation of response to sensory stimuli in (1) children from different ethnicities living within the same geographic and physical environments, (2) children from similar ethnicities and physical environments living in different geographic environments, (3) children from different ethnicities and geographic environments living in similar physical environments, and (4) children from similar ethnicities and geographic environments living in different physical environments.

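### As listed, no comparison matches hypothesis 1: the ethnicity comparison names the same pair of groups as the joint ethnicity-and-geography comparison

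*Protocol article*

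**What the plan says.** The Research Hypothesis section lists four hypotheses. The first is about "children from different ethnicities living within the same geographic and physical environments". The second varies geography alone, the third varies ethnicity and geography together, and the fourth varies physical environment alone.

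The Participants section then assigns groups to four numbered comparisons:

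- The first, labelled as one of ethnicity, takes children "from different ethnicities (Chinese children in Hong Kong, Filipino children in the Philippines-Urban area".
- The second, labelled as one of geography, sets the Filipino group based in Hong Kong against the urban Philippine group.
- The third, labelled as one of ethnicity and geography together, takes children "from different ethnicity and geographic environments (Chinese children in Hong Kong and Filipino children in the Philippines-Urban area".
- The fourth, labelled as one of physical environment, sets the urban Philippine group against the rural one.

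The abstract plans four groups of 32. Besides 32 Chinese children in Hong Kong, these include "32 typically developing Filipino children living in Hong Kong".

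The Background of the Study says that ethnicity will be examined "among a group of children from different ethnicities, while controlling for environment variables". Its next sentence describes how ethnicity is represented: "we recruit Hong Kong-Chinese and Filipino school-aged children living in Hong Kong and the Philippines, respectively".

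The abstract and the Statistical Data section speak of MANOVA on pairwise groupings or combinations. Neither says which groups form the pairs.

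**The concern.** The Background defines geographic environment by country of residence. By that definition, comparison (1) does not hold geography constant, as hypothesis 1 requires. It also duplicates comparison (3), so one pair of groups carries two incompatible labels: ethnicity alone, and ethnicity plus geography.

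An analyst who follows the Participants section literally would report one difference under both labels and would attribute a combined ethnicity-and-country difference to ethnicity. The Background faults earlier work for leaving this ambiguity unresolved, and it suggests that geography may outweigh ethnic influences. The covariate adjustment in the Statistical Data section cannot help within this pair, because every Chinese child in it is in Hong Kong and every Filipino child is in the Philippines.

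**Working it through.** **Step 1. Code the four groups.** Inputs are the group definitions in the abstract. Code ethnicity (Chinese = 1), country (Philippines = 1) and rural setting (rural = 1). Both Hong Kong groups are taken as non-rural, as hypotheses 2 and 3 imply.

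- Chinese, Hong Kong: (1, 0, 0)
- Filipino, Hong Kong: (0, 0, 0)
- Filipino, urban Philippines: (0, 1, 0)
- Filipino, rural Philippines: (0, 1, 1)

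**Step 2. Subtract within each listed pair and compare with the hypothesis.** Signs depend only on the order of subtraction.

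| No. | Hypothesis: what should differ | Listed pair, difference in code | Match |
|---|---|---|---|
| 1 | ethnicity only | (1, 0, 0) − (0, 1, 0) = (1, −1, 0) | no |
| 2 | country only | (0, 0, 0) − (0, 1, 0) = (0, −1, 0) | yes |
| 3 | ethnicity and country | (1, 0, 0) − (0, 1, 0) = (1, −1, 0) | yes |
| 4 | physical setting only | (0, 1, 0) − (0, 1, 1) = (0, 0, −1) | yes |

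Rows 1 and 3 are identical. There are three distinct comparisons for four hypotheses, and none equals (1, 0, 0).

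**Step 3. Find the pair that hypothesis 1 needs.** Only one group is Chinese, so only three pairs vary ethnicity:

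- against Filipino children in Hong Kong: (1, 0, 0)
- against Filipino children in the urban Philippines: (1, −1, 0)
- against Filipino children in the rural Philippines: (1, −1, −1)

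Only the first serves hypothesis 1. Both of its groups are planned, at 32 + 32 = 64 children.

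**Step 4. What comparison (1) estimates as printed.** Write M for a group mean on any outcome. Then

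M(Chinese, HK) − M(Filipino, urban Phil.) = [M(Chinese, HK) − M(Filipino, HK)] + [M(Filipino, HK) − M(Filipino, urban Phil.)].

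The first bracket is the ethnicity difference within Hong Kong, and the second is the country difference among Filipino children. The printed comparison estimates their sum. It can be non-zero when the ethnicity difference is zero, and it can be zero when the two brackets cancel.

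**Step 5. Is ethnicity separable anywhere in the design?** Yes. Comparison (1) minus comparison (2) is (1, −1, 0) − (0, −1, 0) = (1, 0, 0). By the identity in step 4 this is exactly the missing Hong Kong pair. The plan specifies pairwise MANOVAs and no model or contrast that makes this subtraction.

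**Step 6. Does the correction affect the sample size?** Table 2 takes as inputs an effect size f² of 0.0625, 4 groups, 3 response variables, alpha 0.05 and power 0.80. Its output reproduces at N = 88:

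- noncentrality: 3 × 88 × 0.0625 = 16.5
- numerator df: 3 × (4 − 1) = 9
- denominator df: 3 × (88 − 4 + 3 − 3) = 252
- critical F: 1.9171; power: 0.8094

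All agree with the table. The choice of pairs is not among the inputs, so naming a different pair for comparison (1) changes none of these figures.

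**The case against.** The strongest reply is that this is a slip of wording and that the design is sound. Hypothesis 1 is stated correctly, both Hong Kong groups are recruited, and the different labels on comparisons (1) and (3) show that the authors meant two different contrasts. The group list is in the Participants section, whereas the Statistical Data section ties the tests to the research aims through pairwise combinations, which could include the Hong Kong pair.

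Most of this stands, and a slip is the likeliest explanation. It does not remove the point. The general reference to pairwise combinations does not exclude the right pair, but it does not name it either, and the one section that names pairs gives a different one. The Background sentence makes the same mismatch independently, so a slip is likely but not proven.

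A reader might go further and infer that the study will never test hypothesis 1, or cannot address ethnicity at all. The documents do not support that. The confounding is complete within the printed pair but not across the four groups, because Filipino children are sampled in both countries.

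Nor do the documents support inferring that testers differ by country, about which they are silent, or that test-session climate differs. The Procedures and Paradigm section applies the same procedures in both countries, with set ranges for room temperature and humidity. The number of duplicated tests cannot be counted either, because the text does not fix one test per pair per condition.

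**Conclusion.** The point holds as an internal inconsistency that should be corrected before the groups are analysed. As listed, three of the four hypotheses have a matching comparison and hypothesis 1 has none. Comparison (1) repeats comparison (3), and within that pair ethnicity cannot be told apart from country.

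The conclusion rests on the document's own definition of geographic environment as country of residence, and on the Participants section being the only place that assigns groups to comparisons. It is limited to the comparisons as printed. The recruited groups are sufficient to test hypothesis 1 once the right pair is named.

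**What to change.** 1. In Participants, restate comparison (1) as Chinese children living in Hong Kong versus Filipino children living in Hong Kong. Leave the pairs in (2), (3) and (4) as they are.
2. In the Background of the Study, align the sentence that places the two ethnic groups in Hong Kong and the Philippines respectively, so that the ethnicity contrast is described within Hong Kong.
3. Where results are interpreted, treat comparison (3) only as a joint ethnicity-plus-geography contrast and not as evidence for either factor alone. Its present label already says this, so no change of label is needed.

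The cost is a few lines of wording. No further children are needed, and the sample size figures stay as they are. The correction should be made and dated before the group data are examined, because changing the pair afterwards could look like a choice of comparison made with the results in view.

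### The ethnicity and geography hypotheses share one group, Filipino children in Hong Kong, so a shift specific to that group could be declared as both effects

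*Protocol article*

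**What the plan says.** The Abstract (Methods) lists four groups, among them "32 typically developing Chinese children living in Hong Kong" and "32 typically developing Filipino children living in Hong Kong"; the other two are urban and rural Filipino children in the Philippines. There is no Chinese group in the Philippines.

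Research Hypothesis gives these three statements, among others:
- Hypothesis 1: "children from different ethnicities living within the same geographic and physical environments".
- Hypothesis 2: "children from similar ethnicities and physical environments living in different geographic environments".
- Hypothesis 3: "children from different ethnicities and geographic environments living in similar physical environments".

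Participants names the pairs:
- Comparison (1): "from different ethnicities (Chinese children in Hong Kong, Filipino children in the Philippines-Urban area".
- Comparison (2): "from different geographic environments (Filipino children in Hong Kong, Filipino children in the Philippines-Urban area".
- Comparison (3): "from different ethnicity and geographic environments (Chinese children in Hong Kong and Filipino children in the Philippines-Urban area".

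The Abstract and Statistical Data plan MANOVA on HF, LF and EDA for pairwise groupings at a .05 level. Research Aims reads ethnicity as a proxy for genetic influence and environment as a broad measure of culture, parenting, landscape and socioeconomic setting. The demographic variables under Statistical Data and in the Discussion do not name birthplace, length of residence or minority status.

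**The concern.** The study exists to separate ethnicity from environment; the Introduction criticises earlier work for leaving the two entangled. Under the stated hypotheses, both contrasts that are meant to separate them depend on the same group. If that group differs for a reason of its own, such as how families came to be there or the strain of living as a minority, the difference enters contrast 1 and contrast 2 together. It could then be read as genetic in one and as geographic in the other. The article's own allostatic-load framework makes such a shift plausible, since it holds that prolonged exposure can alter autonomic set points.

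Contrast 3 leaves this group out and carries information on the question, but the article states no link between it and the other two.

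**Working it through.** **1. Which pairs test which hypothesis**

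| Hypothesis | Pair that fits Research Hypothesis | Pair printed under Participants |
|---|---|---|
| 1 ethnicity | Chinese-HK vs Filipino-HK | Chinese-HK vs Filipino-Urban |
| 2 geography | Filipino-HK vs Filipino-Urban | Filipino-HK vs Filipino-Urban |
| 3 both | Chinese-HK vs Filipino-Urban | Chinese-HK vs Filipino-Urban |

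For hypothesis 1 the two sections conflict: the printed pair lives in two countries, not one, and it repeats comparison (3).

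**2. Algebra**

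Let e be the ethnicity effect, g the effect of Hong Kong versus the urban Philippines, and m a shift specific to Filipino children in Hong Kong. Relative to Filipino-Urban = 0, the means are Filipino-HK = g + m and Chinese-HK = e + g. Then:
- Contrast 1 (Chinese-HK minus Filipino-HK) = e − m
- Contrast 2 (Filipino-HK minus Filipino-Urban) = g + m
- Contrast 3 (Chinese-HK minus Filipino-Urban) = e + g = contrast 1 + contrast 2

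Three unknowns meet two independent contrasts, so m cannot be identified. If e = g = 0 and m is not 0, contrasts 1 and 2 are −m and +m, with opposite signs, and contrast 3 is 0.

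**3. The plan's own sample sizes**

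The initial size is 32 per group (Participants, effect size 0.8). Table 2 gives 88 in total, or 22 per group. Table 2 reproduces: noncentrality = f² × N × s = 0.0625 × 88 × 3 = 16.5; df 9 and 252; critical F 1.9171; power 0.8094. These figures do not settle the point; they only fix the two group sizes used below.

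**4. Simulation**

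Three groups and three normal outcomes, with two-group Hotelling tests (equivalent to a two-group MANOVA) at .05. The HF–LF correlation was set to −0.7 (assumed); a run with uncorrelated outcomes gave nearly the same results. The shift is a Mahalanobis distance D. The value 0.8 borrows the article's planning effect, which is not an estimate of a shift in this group.

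Shift only in Filipino-HK (e = g = 0):

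| n per group | D | Contrast 1 | Contrast 2 | Contrast 3 | 1 or 2 | Both 1 and 2 |
|---|---|---|---|---|---|---|
| 32 | 0.8 | 74% | 74% | 5% | 88% | 61% |
| 22 | 0.8 | 55% | 55% | 5% | 72% | 37% |
| 32 | 0.5 | 34% | 34% | 5% | 50% | 18% |
| 22 | 0.5 | 23% | 23% | 5% | 36% | 10% |

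**5. Two candidate rules at D = 0.8**

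*Narrow rule:* when 1 and 2 are significant in opposite directions and 3 is not, report a group-specific difference. Direction was taken from the sign of the inner product of the two mean-difference vectors, scaled by the pooled covariance.
- Double declaration under a pure group shift falls from 61% to 3% (n = 32) and from 37% to 2% (n = 22).
- Detection of a true ethnicity-only or geography-only effect falls by about 1 point.
- Trials in which only one of contrasts 1 and 2 is significant are untouched: 88 − 61 = 27% (n = 32) and 72 − 37 = 35% (n = 22).

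*Broad rule:* require a significant contrast 3 before any attribution.
- Detection of a true ethnicity-only effect falls from about 74% to 60% (n = 32) and from about 55% to 38% (n = 22), a loss of 14 to 17 points.
- With e = 0.8, m = 0.8 and g = 0, contrasts 2 and 3 agree, and the rule would certify a geography effect in about 60% (n = 32) or 38% (n = 22) of trials although there is none.

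**The case against.** - **As printed under Participants, the double declaration cannot arise.** There, Filipino children in Hong Kong appear only in comparison (2), and a shift in that group makes the printed ethnicity pair significant about 5% of the time. This stands, and is why the two sections must be reconciled first. It does not rescue the ethnicity claim, because the printed pair differs in country as well as ethnicity.
- **Part of a minority-living effect is environment as defined.** Research Aims includes culture and sociocultural aspects, so crediting some of such a shift to geography in contrast 2 may be legitimate. This stands for contrast 2. It does not justify reading the same shift as ethnicity in contrast 1.
- **Migration history is inferred from residence.** The article does not state birthplace. The algebra needs only a shift specific to the group, whatever its cause.
- **Controls exist.** Socioeconomic variables, resilience and covariate adjustment bear on selection, so contrast 3 is not the only safeguard. None of them measures minority status or length of residence.
- **The study is exploratory, and interpretation rules may sit in a fuller document.** The absence of a rule is therefore not in itself the fault. The shared group is built into the stated hypotheses.

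A reader might go further and infer that one migrant effect would be declared as both effects, or that each attribution should depend on contrast 3. The documents support neither. They give no evidence that such a shift exists or how large it is, and the second rule is costly and can certify a wrong attribution.

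**Conclusion.** The point holds as a limit on interpretation. Under the hypotheses as written, the ethnicity and geography contrasts share Filipino children in Hong Kong, and a shift specific to that group could be declared as both effects. The size depends wholly on an assumed shift: 61% (n = 32) or 37% (n = 22) at D = 0.8, and 18% or 10% at 0.5, with no true ethnicity or country effect. The structural result, that three possible effects cannot be separated from two independent contrasts, needs no such assumption.

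**What to change.** 1. Reconcile comparison (1) under Participants with hypothesis 1, so that comparisons (1) and (3) are no longer the same pair.
2. State that hypotheses 1 and 2 share one group and that contrast 3 is their algebraic sum. If covariates are used, estimate all three from one model so that the sum stays exact.
3. Read the three contrasts jointly, using mean differences with intervals for each outcome, because a multivariate test has no direction of its own.
4. When contrasts 1 and 2 are significant in opposite directions and contrast 3 is not, report a difference specific to Filipino children in Hong Kong, not separate ethnicity and geography effects.
5. When only one of contrasts 1 and 2 is significant, or contrast 3 is significant too, state that a group-specific effect cannot be excluded.
6. Do not make a significant contrast 3 a condition for every attribution.

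The cost is wording fixed before analysis, plus about 1 point of detection for a true single effect. The downside is small: truly opposing ethnicity and geography effects would be reported as not separable, which is all this design can support.

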### Assessments and Measures

#### Behavioral Measures

To measure a child’s behavioral patterns in response to sensory stimulus in his daily activities, the original Sensory Profile [2] and Chinese Sensory Profile [68] are used. The original Sensory Profile, which was developed and validated by Dunn [2], is a 125-item questionnaire that is completed by the caregiver. The Chinese Sensory Profile is a 100-item parent-report measure used among children and uses the same rating scale as the original one. We extracted the similar items from these 2 versions; the computed total and subscale scores will be subjected to intraclass correlation coefficient computation later on. The Sensory Profile has been used in both normative and clinical population in screening for sensory modulation disorders. Higher scores indicate lesser sensory behavior issues, whereas lower scores, typically seen in clinical populations, suggest the prevalence of sensory issues. Because the recruited participants in this study are assumed to be typically developing, statistical analysis may be confounded. We will further use other behavioral measures that can represent behavioral responses. Temperament and resilience were chosen, as this gives unbiased composite scores from which we can ascertain whether sensory behavior responses are deemed to be issues or just a trait pattern.

To measure temperament, the Temperament in Middle Childhood Questionnaire [69] and Early Adolescent Temperament Questionnaire [70] will be used. Both are psychometrically sound measures that are answered by parents to describe their children’s traits [70,71]. We will use the translated and validated Chinese version (personal communication by [name], 2015) for the relevant populations. Three factors will be used in the group analysis: negative effect, surgency, and effortful control.

To measure resilience, the Child and Youth Resilience Measure (CYRM) [72], which was established through a process of interviews with youth and adults in countries around the world, was completed by the participants’ parents. Previous research has suggested that ethnicity and environmental experiences influence the development of resilient behaviors [73,74] and that it is likely moderated by autonomic activity [75-77]. We included resilience as a behavioral outcome measure to determine whether group differences in autonomic activity across conditions can be explained by our main dependent variables (DVs, ie, ethnicity, environment), or other factors, for which we may try to control. This research uses the 28-item (>10 years of age) or the 26-item (5-9 years of age) Person-Most-Knowledgeable questionnaire version, which was developed and validated by Ungar and Liebenberg [78]. The similar items between the 2 versions will be used for analysis. Although CYRM is originally in English, a translated Chinese version was recommended and provided by the authors and was used among Chinese participants in this research (personal communication, [name], 2015).

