#### Statistical Data

Descriptive statistics involving measures of central tendencies, variation, and dispersion are used to describe the salient characteristics of the data gathered. Demographic data related to participant gender, age, BMI, type of school (ie, public, private), number of parents working, primary caregiver, highest educational attainment of caregiver, family income, and parent’s occupation will be gathered and considered in further statistical analyses. The Shapiro-Wilk test of normal is used to determine normality at baseline of the characteristics of the participants included in the study. Univariate and multivariate tests are likewise used to determine whether there are group and subgroup baseline similarities at critical alpha=.05. Variables deemed as non-normally distributed or significantly different at baseline are used as covariates. General linear modeling is used to determine whether effects of ethnicity or environment (used as the independent variables [IV] in this study) can explain differences in the behavioral measures of the participants at a critical value of alpha=.05. Autonomic regulation is represented in this research as HF (n.u.) and LF (n.u.) of HRV and mean EDA (SCL/SCR) values as multivariates. Multivariate analysis of variance (MANOVA) tests will be used to determine whether effects of ethnicity or environment (used as IV in this study) can explain differences in the multivariate set of DVs, across the different research aims, with the different pairwise combinations in between 3 events (resting baseline, stimulation, and recovery). Effect size is interpreted using the values of Cohen *d*. Statistical analysis will be computed using SPSS version 23.0.

Specific to this report, sample size and power analysis are performed using G*Power version 3.1.9.2 [91,92]. Post hoc analysis of computed achieved power of the pilot data will be ascertained to determine the needed effect size for a subsequent a priori computation of required sample size for MANOVA tests.

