## Discussion

Our initial data suggest that ample sample size is needed to demonstrate our concepts and prove our hypothesis, given our methods. Although our initial findings currently yield nonsignificant results, the lack of differences in the regulation of response between our sampled groups might be due to underpowered sample size; hence, the researchers shall be guided with the recommended ample sample size in the offing.

Although there is much that remains to be done, our work has future important findings in the field. The development of the ability to regulate responses to sensory stimuli does not occur in a vacuum, and some other variables (ie, cultural, anthropological, socioeconomic) may likely account for variations. Although we will collect several measures of socioeconomic status (ie, school attended, whether public or private; number of parents working; primary caregiver; highest educational attainment of caregiver; family income; and parent’s occupation) and proxy cultural measures (ie, parent-reported behavioral profiles of the child) and try our best to control for their confounding effects through sample stratification and statistical measures, their main effects are beyond the scope of this research. In this research, we mainly aimed to explore the influence of ethnicity and environment to explain differences in the regulation of response to sensory stimuli among typically developing school-aged children through indexing physiological autonomic measures from a biomedical and neurophysiological perspective.

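### The protocol treats resilience and other parent-reported behavioural scores as outcomes of ethnicity and environment, yet also proposes to control for them in the autonomic comparisons, without saying which analysis decides the hypotheses

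*Protocol article*

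**What the plan says.** **Scores as outcomes.** Methods, Behavioral Measures, says of resilience (CYRM): "Previous research has suggested that ethnicity and environmental experiences influence the development of resilient behaviors", and adds that "it is likely moderated by autonomic activity". It then says: "We included resilience as a behavioral outcome measure to determine whether group differences in autonomic activity across conditions can be explained by" ethnicity and environment. Statistical Data plans a general linear model to see whether ethnicity or environment "can explain differences in the behavioral measures of the participants". There the behavioural scores are dependent variables.

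**Scores as something to control.** The resilience sentence continues that the purpose is to learn whether autonomic group differences come from ethnicity and environment "or other factors, for which we may try to control". The Discussion is firmer. Alongside the socioeconomic variables it names "proxy cultural measures (ie, parent-reported behavioral profiles of the child) and try our best to control for their confounding effects", to be done by stratifying the sample and by statistical means. The CYRM, temperament and Sensory Profile scores are all reported by a parent or caregiver.

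**What is to be tested.** Research Question and Motivation, and Research Hypothesis, ask whether ethnicity and environment influence regulation of the response, through four group contrasts. Research Aims defines environment broadly, with behaviours, culture and parenting practices inside the definition.

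**The autonomic model.** Statistical Data names a MANOVA on HF, LF and EDA. Its covariate rule brings in variables that are non-normal or differ significantly at baseline. It does not mention the behavioural scores in either direction.

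**The concern.** A variable that the exposure changes is not a confounder of that exposure's effect. The protocol says that ethnicity and environment shape resilience, and that resilience is tied to autonomic activity. Holding resilience fixed therefore changes the question from whether the groups differ to whether children with equal resilience differ between groups.

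The consequence depends on the causal direction, which the protocol leaves open. If resilience carries part of the environmental effect to the autonomic system, adjustment removes a real effect, which might then be credited to other factors. If autonomic activity shapes resilience, adjustment can produce a group difference in HF, LF or EDA where there is none in total. For the environment contrasts there is a further difficulty: controlling for proxies of culture and behaviour takes out part of what Research Aims counts as environment.

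Because the control is worded as optional, the choice between adjusted and unadjusted results could also be made after both are seen.

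**Working it through.** **1. Figures in the protocol.** None bears directly on this point, because its sample-size work includes no covariates. Table 2 reproduces: f² = 0.0625, 4 groups, 3 outcomes and N = 88 give λ = 3 × 88 × 0.0625 = 16.5, df 9 and 252, and power 0.8094. The initial basis (Participants: d = 0.8, 32 per group, alpha .05, two-sided assumed) gives power 0.88 for one outcome by the noncentral t. That is the reference value for step 3.

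**2. What adjustment does.** In within-group SD units, let c be the total group difference in an autonomic measure, dM the group difference in the behavioural score, and r their within-group correlation. Then:
- adjusted difference = c − r × dM
- standard error = √(1 − r²) × √(2/n + dM²/(2n − 2)), with 2n − 3 df

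This algebra needs only the correlation, not a causal direction. The protocol gives neither dM nor r, so both are assumed below: dM 0.5 to 0.8, r from −0.5 to 0.5.

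**3. One outcome, 32 per group.** Example with c = 0.8, dM = 0.8, r = 0.5: 0.8 − 0.5 × 0.8 = 0.40; SE = 0.866 × √(0.0625 + 0.0103) = 0.234; ratio 1.71; power 0.39.

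| dM | r | Tested difference, c = 0.8 | Power (0.88 unadjusted) | Tested difference, c = 0 | Rejection (5% unadjusted) |
|---|---|---|---|---|---|
| 0.5 | 0.3 | 0.65 | 0.74 | −0.15 | 9% |
| 0.8 | 0.3 | 0.56 | 0.57 | −0.24 | 15% |
| 0.5 | 0.5 | 0.55 | 0.68 | −0.25 | 20% |
| 0.8 | 0.5 | 0.40 | 0.39 | −0.40 | 39% |

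With r = 0 the difference does not move. With r = −0.5 and dM = 0.8 it grows from 0.8 to 1.20.

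**4. Three outcomes, as in the planned two-group MANOVA.** Assume no group difference in HF, LF or EDA, an HF–LF correlation of −0.7, EDA independent, and a score that correlates r with HF and is linked to LF only through HF. The adjusted test is then an F with 3 and 2n − 5 df and noncentrality

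λ = dM² × r²/(1 − r²) ÷ [2/n + dM²/(2n − 2)].

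For 32 per group:
- dM = 0.8, r = 0.3: 0.64 × 0.0989 ÷ 0.0728 = 0.87, rejection 10%
- dM = 0.8, r = 0.5: 0.64 × 0.3333 ÷ 0.0728 = 2.93, rejection 25%
- dM = 0.5, r = 0.3: 0.25 × 0.0989 ÷ 0.0665 = 0.37, rejection 7%
- dM = 0.5, r = 0.5: 0.25 × 0.3333 ÷ 0.0665 = 1.25, rejection 13%
- dM = 0.8, r = 0.2: 0.64 × 0.0417 ÷ 0.0728 = 0.37, rejection 7%

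At 22 per group the first two become 8% and 18%. Simulation of those two settings at 32 per group agrees (about 10% and 25%), with the unadjusted test near 5%.

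These rates are false positives for the total group difference, which the hypotheses concern. For the conditional null the adjusted test keeps its 5% level.

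**The case against.** The strongest reply is that the analysis section never puts these scores into the autonomic test. Statistical Data names a MANOVA, the variables it carries into further analyses are demographic, and the behavioural scores appear there only as dependent variables. The one adjusted model actually run, the pilot MANCOVA, used BMI alone. The resilience sentence is conditional, the Discussion sentence specifies no model, and a condensed article may leave covariate lists to a fuller plan. This stands against a stronger reading that a reader might infer, namely that the planned hypothesis test is adjusted for behaviour and so tests the wrong null. The text does not say that. It does state an intention to control for these scores, and nothing in Statistical Data rules it out.

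Second, the protocol asserts an effect of ethnicity and environment only for resilience. For temperament and the Sensory Profile it merely tests for group differences. The wording on autonomic activity speaks of moderation, which is not the same as autonomic activity causing resilience. Both points stand and limit what can be said about cause; the shift of −r × dM does not depend on them.

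Third, this is an exploratory, non-randomised, cross-sectional study. For the ethnicity contrast, with ethnicity taken as a proxy for genetic influence, a comparison conditional on cultural proxies is a coherent secondary question. An unadjusted MANOVA does not isolate influence either. This also stands, and is why an outright ban on adjusted models is not warranted. It is weaker for the environment contrasts, where culture and behaviour belong to the exposure as defined.

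**Conclusion.** The point holds as an unresolved conflict of roles: the same scores are outcomes under Behavioral Measures and Statistical Data, and factors to control under Behavioral Measures (conditionally) and the Discussion (as an intention). Following the Discussion as written would move the tested difference away from the stated hypotheses.

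The size cannot be determined from the protocol. Over the assumed range at 32 per group, the three-outcome test rejects about 7% to 25% of the time when there is no total difference, and one-outcome power at d = 0.8 falls from 0.88 to between 0.74 and 0.39 for positive r. The distortion is small if dM or r is small and vanishes at r = 0. For a given dM its direction depends on the sign of r. The multivariate figures also rest on the assumed correlation structure.

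**What to change.** Three changes of wording:

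1. **Statistical Data:** state that the four hypotheses are decided by the MANOVA or MANCOVA without CYRM, temperament or Sensory Profile scores as covariates, and that the covariate rule does not extend to them. They stay as outcomes in the general linear model already planned.
2. **Discussion:** take the parent-reported behavioural profiles out of the list of confounders to be controlled.
3. **Behavioral Measures (resilience):** label any behaviour-adjusted autonomic model as exploratory and not deciding the hypotheses.

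No new data or participants are needed, and a formal mediation analysis is not required. The cost is giving up any variance reduction these scores might bring to the main test.
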